#### 2.5.1. Randomization

We will use two levels of randomization. Teams will be generated using an online balanced team generator [39]. For each trial center, a stratification by professional status will be made in order to be representative of the current practice in the field with at least one paramedic per team. In teams made up of an EMT and a paramedic, the paramedic will always be the “team leader”. In teams made up of two paramedics, they will choose their role, as in actual clinical practice.

The teams will then be randomized in one of the two study arms by opening an opaque, sealed envelope containing the approach to apply (standard or experimental) created using a stratified randomization list generated online by [name] ([name]) using a 1:1 ratio [40]. The actual standard 30:2 approach may be slightly different between the EMSs, for instance regarding service-specific task distribution, quality processes, prior specific training or local procedures during CPR. To take into account such discrepancies, a randomization stratified by service will be used.

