### 2.7. Outcomes

The primary outcome will be the chest compression fraction (CCF) during the first two minutes of CPR (starting from first compression).

Secondary outcomes will be: CCF of each following 2 min cycle (from minutes 2 to 4, 4 to 6, 6 to 8 and 8 to 10), overall CCF (entire 10 min scenario), chest compressions depth; proportions of compressions within the depth target (5 to 6 cm), below target value (<5 cm) and above target value (>6 cm); chest compressions rate; proportions of compressions within the appropriate rate target (100 to 120 compressions per minute (cpm)), below target value (<100 cpm) and above target value (>120 cpm); proportions of compressions with complete chest recoil (<5 mm deviation from the reference value); time to first shock; time to first effective ventilation (defined as >300 mL [47,48,49,50,51]); ventilations volume; proportions of ventilations above target value (>700 mL), below target (<300 mL) and within target (300–700 mL); number of delivered ventilations; user satisfaction, and providers’ self-assessed cognitive load.

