All data that could allow the data analyst to identify the group allocation will be deleted (e.g., number of insertion attempts). The groups will be renamed otherwise (groups “Teysachaux” and “Moléson”) and the curated database will be sent in Stata DTA file format to DT for formal analysis. All investigators will be able to access the curated and coded data set.

Distribution normality will be checked graphically for continuous variables, and the Shapiro–Wilk test will be used in case of doubt. If this assumption is checked, a Student’s t-test will be used to compare both groups; if not, the Mann–Whitney U test will be used. These variables will be described using mean (SD) or median (Q1; Q3) depending on their distribution. We will test proportions using Fisher’s exact test. They will be reported with their 95% confidence interval.

User satisfaction will be assessed graphically, then dichotomized into “Satisfied” versus “Not satisfied” before being tested using Fisher’s exact test. The cognitive load variable will be treated as continuous.

A two-sided p-value of 0.05 will be considered significant. All the statistical analyses will be performed using Stata V15.1 (StataCorp. 2017. Stata Statistical Software: Release 15. College Station, TX: StataCorp LLC).

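### The rule that tests proportions with Fisher's exact test does not fit the ten compression and ventilation proportions, because the randomised unit is the team

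*Protocol article*

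**What the plan says.** Section 2.9 of the protocol article gives two general rules. Continuous variables go to a t-test, or to a Mann-Whitney test if they are not normal. For proportions the rule is: "We will test proportions using Fisher’s exact test. They will be reported with their 95% confidence interval". No unit of analysis is attached to it.

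Section 2.7 uses the same word for ten secondary outcomes:

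- Depth, three outcomes: "proportions of compressions within the depth target (5 to 6 cm), below target value (<5 cm) and above target value (>6 cm".
- Rate, three outcomes, beginning with "proportions of compressions within the appropriate rate target (100 to 120 compressions per minute (cpm", then below and above that range.
- Recoil, one outcome: "proportions of compressions with complete chest recoil (<5 mm deviation from the reference value".
- Ventilation volume, three outcomes: above, below and within the 300 to 700 mL range.

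Dichotomised satisfaction has a sentence of its own: "User satisfaction will be assessed graphically, then dichotomized into “Satisfied” versus “Not satisfied” before being tested using Fisher’s exact test". Section 2.5.1 fixes the randomised unit: "The teams will then be randomized in one of the two study arms". Section 2.9 plans 24 teams.

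**The concern.** Fisher's exact test compares counts of independent units in a contingency table. A team's percentage of compressions at the right depth is not such a count. The test can be run on these outcomes only by adding up single compressions or ventilations over all teams in an arm. All events of a team come from the same two people on one manikin in one ten-minute session, so they are correlated. Treating them as independent replaces 12 teams per arm with thousands of events.

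Satisfaction is covered separately, and section 2.7 lists no other outcome that is binary per team or per participant. The general sentence therefore has no evident outcome to govern except these ten. They carry much of the secondary objective in section 1.2, which is to compare the quality of basic life support between the approaches. If the sentence were followed literally, the p-values would be too small and the confidence intervals too narrow.

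**Working it through.** **The plan's own figure.** The protocol gives no figure for the secondary proportions. Its one calculation is for the chest compression fraction (CCF), with means 77 and 93, SD 12, 90% power and two-sided 5%:

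n per arm = 2 × (1.960 + 1.282)² × 12² / 16² = 11.8, so 12 per arm and 24 teams.

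This reproduces the stated 24 (normal approximation). It also shows that CCF, itself a proportion of time, is planned as one continuous value per team.

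**Events per team, if events were pooled.**

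- Compressions: 10 min (section 2.5.4) × 100 to 120 per minute (section 2.7) × CCF 0.77 to 0.93 (section 2.9). The low end is 10 × 100 × 0.77 = 770 and the high end is 10 × 120 × 0.93 = 1,116. I use m = 900, which is 12 × 900 = 10,800 per arm.
- Ventilations: assumed 50 to 90. Two ventilations five times per two-minute cycle (section 2.9), carried over five cycles, give 50. Ten per minute (section 2.5.5) for about nine minutes, after roughly 60 s to the first one (section 1.1), give 90.

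**Formulas.** Design effect DE = 1 + (m − 1) × ICC. The pooled standard error is too small by a factor √DE. The actual type I error of a nominal 5% test is 2 × (1 − Φ(1.96/√DE)). The ICC is not in the documents, so it is an assumption shown over a range.

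| Outcome | m | ICC | DE | √DE | Type I error |
|---|---|---|---|---|---|
| Compression | 900 | 0 | 1.0 | 1.0 | 5% |
| Compression | 900 | 0.01 | 10.0 | 3.2 | 54% |
| Compression | 900 | 0.05 | 46.0 | 6.8 | 77% |
| Compression | 900 | 0.10 | 90.9 | 9.5 | 84% |
| Compression | 900 | 0.30 | 270.7 | 16.5 | 90% |
| Ventilation | 50 | 0.05 | 3.45 | 1.9 | 29% |
| Ventilation | 90 | 0.10 | 9.9 | 3.1 | 53% |

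Using 770 or 1,116 instead of 900 moves the 77% to 75% or 79%.

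**Where the error passes one half.** This needs DE above (1.96/0.6745)² = 8.4. That is an ICC of about 0.008 at m = 900, but about 0.10 at m = 75.

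**A rough anchor for the ICC.** Borrow the protocol's SD of 12 points for CCF as the between-team SD of another proportion p (an assumption). Then ICC = 0.12²/(p(1 − p)), which is 0.058 at p = 0.5 and 0.09 at p = 0.8. The type I error is then about 79% to 83% for compressions (m = 900) and 39% to 48% for ventilations (m = 75).

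**Simulation.** Beta-binomial data were generated with no difference between arms, 12 teams per arm, p = 0.5 or 0.8, and ICC from 0 to 0.30. Fisher's test on pooled counts matched the table within simulation error. With one percentage per team, the t-test and the Mann-Whitney test rejected in 4% to 5% of runs in every setting (20,000 runs each).

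**The case against.** A reader might infer that the plan treats some 900 compressions per team as independent, and that most secondary quality outcomes will come out falsely significant. The documents do not support either statement.

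On the first, no section says that single events are the unit of analysis. CCF is handled per team. Section 2.9 has a script derive the variables of interest before import, which fits team summaries at least as well as raw events; that script is a supplement not shown here. Fisher's test may have been meant for categorical variables such as gender and professional title, with per-team percentages going to the continuous-variable rule. A separate analysis plan, if there is one, may say so.

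On the second, section 2.7 contains 14 compression and ventilation quality outcomes: the ten proportions plus depth, rate, volume and number of ventilations. At ICC 0.05 with no true differences, and about 35% for a ventilation proportion, the expected number of false positives is 7 × 0.77 + 3 × 0.35 + 4 × 0.05 = 6.6 of 14, just under half. It depends wholly on an ICC that the protocol does not give.

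Both parts of this objection limit the point but do not remove it. The benign reading has to set aside the sentence as written, because section 2.7 applies the word proportions to exactly these outcomes. This is a named test that does not fit, rather than a detail left for later.

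**Conclusion.** The rule is wrong as written, and it affects secondary outcomes only. As worded, it assigns to seven compression and three ventilation proportions a test that cannot use one value per team and that is invalid on pooled events. The consequence is conditional: the inflation in the table arises only if events are pooled, and its size rests on the assumed ICC and, for ventilations, on the assumed 50 to 90 per team. At ICC 0 there is none, though that would require all teams within an arm to have the same underlying proportion.

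The following are not affected: the primary outcome, the 24-team sample size, the other CCF outcomes, mean depth, rate and volume, the number of ventilations, and the times to first shock and first effective ventilation.

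**What to change.** Replace the sentence on proportions in section 2.9 with text to this effect: *Each proportion of compressions or ventilations is summarised as one percentage per team. These percentages are compared between arms as continuous variables (n = 24 teams) with the t-test or Mann-Whitney test specified above, and reported with a team-level 95% confidence interval. Fisher's exact test is used for genuinely categorical variables, such as dichotomised satisfaction.*

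The satisfaction sentence can stay as it is, and no new model is needed because both tests are already in the plan. The cost is a short change of wording and confidence intervals wider than pooled counts would give. That extra width reflects the 24 randomised teams.

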## 3. Results, Ethics and Dissemination

### 3.1. Research Ethics Approval

The study has been submitted to the regional Ethics Committee (REQ-2020-01491), which stated that the need for approval was waived, as this study does not come into the scope of the Swiss federal law on human research [53]. The study will be conducted in accordance to the principles of the Declaration of Helsinki and Good Clinical Practice guidelines [54,55]. All participants will sign an informed consent form before randomization (Supplementary Files S8 and S9).

### 3.2. Protocol Version

The actual protocol version is 1.0 (22 February 2021). Study sessions are scheduled for March and May 2021.

### 3.3. Trial Registration

This study is registered on https://clinicaltrials.gov/ (accessed on 23 February 2021) under trial registration number NCT04736446.

### 3.4. Data Curation and Availability

The results, either positive or negative, will be submitted for publication in a peer-reviewed journal following the CONSORT statement [36]. The curated database will be deposited on Mendeley Data [56]. The original documents and files will be kept in a safe place. One investigator (DT) will be responsible for data and files storage from all centers for 10 years.

### 3.5. Consent or Assent

Information regarding the study and its objectives (without detailed outcomes), including data security, will be provided. Written consent will be gathered. All the documents will be written in French (Supplementary Files S3 and S8 and Supplementary Tables S5 and S6). Participation will be free and each participant will be able to withdraw at any time without giving any justification. The benefit obtained by the participants will be an increase in knowledge of the i-gel^®^ device’s use, which could be useful in their practice. There will be no financial compensation.

## 4. Discussion

The main limitation of this study is that it will be performed on a manikin, and that there will therefore be no direct evidence regarding actual clinical outcomes. Nevertheless, it is reasonable to assume that, if the CCF can be improved on a manikin, the same should hold true in an actual OHCA situation. However, the main difference between simulated and actual OHCA could rely on device insertion rate. Thus, should increases in the CCF be proven in this study, a further step could be a trial conduct in the field.

Due to the type of intervention, the blinding of participants to their allocated group will not be possible. Participants will, however, remain unaware of the study outcomes. Moreover, an objective measure of the main outcomes will be used continuously during the intervention to allow reliable assessment. The voluntary recruitment strategy could bias the sample, via a self-selection phenomenon which would give an unrepresentative sample of participants (with only those who are the most confident, motivated and involved that will take part in the study).

The seal pressure appears to improve over time in a number of humans due to the thermoplastic properties of the gel cuff [27], which may form a more efficient seal around the larynx after warming to body temperature. In this study, we will not expect such a good sealing because the manikin will not reach the appropriate temperature. This could make the manikin more difficult to ventilate.

The scenario represents one of the various contexts of OHCA: for instance, no first responder or medical reinforcement will be present on scene, and therefore the cardiopulmonary resuscitation will be managed with only two healthcare providers. This could impact several aspects of the secondary outcomes, due to fatigue or specific organization, and therefore limit the generalization of the results.

High-fidelity manikins provide a realistic and high-yield immersive environment. They have been shown to induce an increase in physiological and psychological stress parameters [57,58] during emergency training sessions [59] without affecting the quality of cardiopulmonary resuscitation [60]. In addition, the experimental approach will be new to the participants, thereby further increasing their stress level. Therefore, adding other external stressors should not significantly affect the outcomes of this study, but might impede learning. Indeed, new learners initially benefit from a less stressful simulation environment before being confronted with a gradual increase in stress demands through clinical practice [61], or by virtue of progressive simulations [62]. Moreover, should further studies prove the addition of external stressors to be a confounding factor, the random allocation of participants should markedly dampen any effect this factor might have.

The strengths of this trial are the multicenter design, including paramedics and EMTs from several EMS of Switzerland, which, by comparing two feasible and clinically relevant treatment strategies, addresses an evidence gap regarding the optimal approach, especially in the initial airway management of OHCA, developed in accordance with the SPIRIT guidelines. The results of the study could support the external validity and implementation of this experimental approach in the field.

## 5. Conclusions

This study should help to determine whether early use of an i-gel^®^ with continuous manual compressions could increase CCF compared to the 30:2 approach.

## Figures and Tables

**Figure 1 healthcare-09-00354-f001:**
[figure not shown]
Study flow chart.

**Figure 2 healthcare-09-00354-f002:**
[figure not shown]
Study sequence.

**Table 1 healthcare-09-00354-t001:** Timeline of enrolment, interventions and assessments.

	STUDY PERIOD					
	Enrolment	Workshop	Training Session	Allocation	Post-Allocation	Close-Out
TIMEPOINT	t-3 _before study day_	t-2 _-40 min_	t-1 _-20 min_	t0	t1	t2
**ENROLMENT:**						
**Eligibility screen**	X	X				
**Randomization into pairs**	X					
**Informed consent**		X				
**Standardized workshop**		X				
**Training session**			X			
**Allocation**				X		
**INTERVENTIONS:**						
**Standard approach**					X	
**Experimental approach**					X	
**ASSESSMENTS:**						
***Age, gender, years of experience, profession title, estimated insertions on manikin, estimated insertions on real patients***		X				
***CCF, compressions depth and rate, chest recoil, time to first shock and to first ventilation, number and volume of ventilations.***					X	
***User satisfaction, cognitive load***						X

## Data Availability

No new data were created or analyzed. Data sharing is not applicable to this article. Data that will be generated in this coming study will be freely available on Mendeley Data.
